### Candidate variables for inclusion in the model

Candidate predictor variables will be obtained from patient demographic characteristics and from clinical assessment including clinical history, examination and investigations. The predictors will be clearly defined and standardised to ensure reproducibility and enhance generalisability and application of study results to practice. Data will also be collected on any interventions applied between recruitment and outcome onset that may modify the outcome.

We will choose the candidate predictors a priori to be considered in the prediction model, based on the most promising predictor variables as identified with our previous systematic review [17–22]. The full list of variables to be evaluated for prediction of maternal and fetal outcomes is provided in Table 2.

**Table 2 Tab2:** List of candidate predictor variables to be evaluated in the PREP study

Maternal characteristics Maternal age at diagnosis (years) Gestational age at diagnosis (weeks) Number of fetuses in pregnancy at time of consent (1, 2, 3)
History Summary score for medical history—1 point for each of the following: pre-existing hypertension, renal disease, diabetes mellitus, autoimmune disease, previous history of pre-eclampsia (0, 1, 2 or more)
Symptoms Headache and/or visual disturbance (yes/no) Epigastric pain, nausea and/or vomiting (yes/no) Chest pain and dyspnoea (yes/no)
Bedside examination and tests Systolic blood pressure (mmHg, highest measurement over 6 h) Diastolic blood pressure (mmHg, highest measurement over 6 h) Clonus (yes/no) Exaggerated tendon reflexes (yes/no) Abnormal oxygen saturation (<95% on air) (yes/no) Urine dipstick (0, 1+, 2+, 3+, 4+ or more)
Laboratory tests Haemoglobin (g/L) Platelet count (× 10^9^/L) ALT (IU/L) Serum uric acid (μmol/L) Serum urea (mmol/L) Serum creatinine (μmol/L) Urine protein-creatinine ratio (PCR) (mg/mmol)
Management at baseline Administration of oral and/or parenteral anti-hypertensives (ongoing or commenced within 1 day of diagnosis) (yes/no) Administration of magnesium sulphate (commenced before or within 1 day of diagnosis) (yes/no)
Additional factors for fetal model only Uterine artery Doppler (normal/abnormal) Liquor volume (normal/abnormal) CTG findings (normal/abnormal) Estimated fetal weight <10th centile (yes/no)

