### Sample size considerations

From our systematic reviews [17], 20% of women with early-onset pre-eclampsia are expected to have adverse maternal outcomes at any time before discharge. Rules of thumb for fitting multivariate models suggest about 10 events for every variable are required to reduce issues with overfitting, and we will work within this constraint [24–26]. We initially planned to examine 10 predictor variables and hence planned to recruit 500 women. However, the event rate was lower than predicted, so we revised our plan to recruit sufficient women to obtain 100 events. Subsequent to the inclusion of delivery before 34 weeks as a component of the composite outcome, we revised our plan to include 22 candidate predictor variables, which was approved by the independent study Committees.

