### Statistical analysis

We will develop two prediction models: a survival model for adverse maternal outcomes at various time points from diagnosis up to 34 weeks of gestation, including by 48 h after admission, and a logistic model for adverse maternal outcomes by discharge. These will both be developed using a general methodological and statistical framework as outlined below.

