#### Model development, apparent performance assessment and internal validation

The predictors of adverse maternal outcomes will be identified to develop and externally validate a simple, interpretable and clinically applicable prediction model with face validity. We will use a transparent process that implements appropriate statistical methods and adheres to current methodological recommendations.

A backwards selection procedure will be used to decide which of the candidate predictor variables should be included in the final prediction model (with *p* < 0.15 taken conservatively to warrant inclusion). Continuous variables will be kept as continuous in the model (rather than dichotomising), to avoid a loss of power [27, 28]. Non-linear trends will also be considered using the multivariable fractional polynomial procedure [29, 30], which uses multivariable models to eliminate weaker predictors and identify transformations of continuous predictors that best predict outcome. Large amounts of missing variable data are not expected, but some will inevitably occur, with not all patients providing all variables of interest. Multiple imputation will be used to impute, with 5 imputations, under a missing at random assumption, missing values so as to avoid excluding patients from the analysis [27].

For survival analysis, failure event is defined as an adverse outcome or delivery occurring before 34 weeks of gestation. We will use a flexible parametric survival model via the Royston-Parmar approach [31–33], with the cumulative baseline hazard scale modelled using restricted cubic splines. The number of knots will be chosen by visual inspection. For the binary adverse maternal outcome by discharge, a logistic regression-modelling framework will be undertaken with the logit probability of an adverse outcome being the response variable.

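### Table 2 enters oxygen saturation only as a yes/no variable cut at 95%, against the article's own rule that continuous predictors stay continuous, and gives no reason for the exception

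*Protocol article*

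**What the plan says.** Under Candidate variables for inclusion in the model, Table 2 groups saturation with the bedside examination and tests, as "Abnormal oxygen saturation (<95% on air) (yes/no". In the same group, systolic and diastolic pressure are listed in mmHg. All seven laboratory tests are listed in their own units.

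The section on model development, apparent performance and internal validation states: "Continuous variables will be kept as continuous in the model (rather than dichotomising), to avoid a loss of power". It adds: "Non-linear trends will also be considered using the multivariable fractional polynomial procedure". The Statistical analysis section introduces two models, both for maternal outcomes (a survival model and a logistic model by discharge), and says of them: "These will both be developed using a general methodological and statistical framework as outlined below".

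For the fetal model only, Table 2 lists "Estimated fetal weight <10th centile (yes/no".

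No reason is given for either cut-point. The article does not report how saturation is distributed, what share of women fall below 95%, or how risk changes with saturation.

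**The concern.** The rule against dichotomising comes with its reason, loss of power, and that reason applies to saturation as much as to blood pressure or platelets. A percentage must be read before anyone can say it is below 95%, so the continuous value exists at the bedside.

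With the yes/no form, all readings of 95% and above are treated alike, as are all readings below 95%, and predicted risk jumps at the cut. If few women are below the cut, the term is sparse and is more easily dropped by backward selection.

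Saturation is also close to the outcome. The maternal composite in Table 3 includes pulmonary oedema, one definition of which uses a saturation criterion, and a need for a high oxygen concentration for more than an hour. A predictor tied to the cardiorespiratory components deserves the treatment the plan gives the other measurements.

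**Working it through.** **1. The article's own figures.** Inputs from Sample size considerations: "20% of women with early-onset pre-eclampsia are expected to have adverse maternal outcomes at any time before discharge"; "about 10 events for every variable are required to reduce issues with overfitting"; "We initially planned to examine 10 predictor variables and hence planned to recruit 500 women".

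N = predictors × events per variable / event rate = 10 × 10 / 0.20 = 500 women, or 100 events. This reproduces the stated figure. The article later replaced 500 women with recruitment to 100 events, and then moved to 22 candidates.

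Maternal candidates in Table 2: characteristics 3 + history 1 + symptoms 3 + bedside 6 + laboratory 7 + management 2 = 22, which matches the stated number. Saturation counts as one of them. As a single linear term it still counts as one.

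**2. Information kept by a cut, for a normal predictor with a linear effect.** Let p be the share of women below the cut, z its normal quantile and φ the normal density. The share kept, relative to a linear term, is φ(z)² / [p(1 − p)]. For p = 0.05: z = −1.645, φ = 0.1031, and 0.1031² / (0.05 × 0.95) = 0.224, so 78% is lost. The values of p are assumptions.

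| Share below cut | Kept | Lost |
|---|---|---|
| 1% | 7% | 93% |
| 2% | 12% | 88% |
| 5% | 22% | 78% |
| 10% | 34% | 66% |
| 20% | 49% | 51% |
| 30% | 58% | 42% |
| 50% | 64% | 36% |

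**3. Distributions nearer to real saturation (all assumed).** Values are whole numbers capped at 100. The share kept is the squared correlation between the yes/no variable and the percentage.

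| Assumed distribution | Share below 95 | Lost |
|---|---|---|
| Mean 97, SD 1.5 | 4.8% | 77% |
| Mean 97, SD 2 | 10.6% | 61% |
| Mean 96, SD 2 | 22.7% | 46% |
| 98% of women around 98 (SD 1), 2% around 91 (SD 2) | 1.9% | 53% |
| 95% around 98, 5% around 91 | 4.8% | 33% |
| 90% around 98, 10% around 91 | 9.6% | 23% |

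A distinct low-saturation subgroup therefore reduces the loss considerably. With about 2% or more of women below the cut, and no threshold effect, the scenarios for saturation run from 23% to 88%. A rarer cut would lose more (93% at 1% in the first table).

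**4. Logistic check by simulation.** 200,000 simulated women, normal predictor, intercept −1.386 (20% risk).

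- True effect linear, 0.4 on the log-odds scale per SD: the yes/no term keeps 27%, 41% and 63% of the linear term's likelihood-ratio chi-square at p = 5%, 10% and 30%.
- True effect a step of 0.8 on the log-odds scale at the cut: the ratio reverses. The yes/no term has 4.1, 2.7 and 1.7 times the chi-square of the linear term.

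**5. Fetal weight.** By the formula in step 2, the loss would be 66% if 10% of fetuses fall below the 10th centile and 42% to 36% if 30% to 50% do. These shares are assumed.

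**The case against.** The strongest reply is that the two sections can be read together. Predictors were to be chosen in advance and given standard definitions; those listed in units stay continuous, and those defined as yes/no are binary. On that reading the rule governs only variables that enter as continuous. This softens the conflict but does not remove it: nothing in Table 2 says that saturation is collected only as a category, and the exception is neither named nor explained.

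A reader might infer that most of the predictor's information is certainly thrown away. The documents do not support that. It needs a roughly linear effect and a low share of women below the cut without a distinct low subgroup, and the article reports none of these. If risk steps at 95%, the binary form is the better one, and a smooth fractional polynomial would not fully reproduce a step. The article, however, claims no such threshold.

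A reader might also infer that the fetal-weight cut breaks the same rule. It does not. The framework containing the rule is written for the two maternal models, the modelling of the secondary fetal outcome is not described in the article, and a centile is already relative to a reference.

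Two further points stand. Women with any outcome before testing are excluded, which removes some of the very low readings; this narrows the contrast within the yes group and also makes that group rarer. And a count of yes-carriers based on 500 women would rest on a superseded sample size.

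**Conclusion.** The coding of saturation in Table 2 departs from the article's stated rule without justification, and the two places should be reconciled. The loss cannot be fixed from the documents. It is about 23% to 88% of this one predictor's information in the scenarios of the working, and none if risk steps at 95%. All of these figures rest on assumed distributions and effect shapes.

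The effect on the C-statistic was not estimated, and no bias is shown. With one of 22 maternal candidates affected, the impact is modest. The change is still worth making, because the plan's own reason calls for it. The fetal-weight coding is a parallel weakness in a secondary model and is not needed for this conclusion.

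**What to change.** In Table 2, replace the yes/no row with oxygen saturation on air (%), and model it as a continuous term under the stated selection and fractional-polynomial procedure. Use the form cut at 95% only where no raw value exists, for example in an external validation cohort. If the yes/no form is kept on purpose, say so in the text and give the reason.

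The candidate count stays at 22 and the event target does not change. There are two costs. A fractional polynomial may use an extra degree of freedom, as it may for every other continuous candidate. If only yes/no was recorded for women already recruited, the readings would have to be taken from the notes at the sites; multiple imputation could not supply them unless enough women had an observed value.

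For the fetal model, consider entering estimated fetal weight as a centile or z-score on the same grounds.

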### Objectives

The primary objectives are to develop and internally validate a prediction model in women admitted with early-onset pre-eclampsia from 20 weeks and 0 day to 33 weeks and 6 days of gestation, for assessment of the risk of adverse maternal outcomes at 48 h and by discharge. The 48 h of time interval was chosen to reflect the time recommended for delivery after administration of steroids to lower risks of respiratory distress in newborns. This time period is also considered to be the optimal duration to make decisions on timing and place of delivery and consider in utero transfer to a tertiary care unit if needed. The model will be externally validated in two independent datasets of patients with a diagnosis of early-onset pre-eclampsia. Our secondary objective is to assess the risk of adverse fetal and neonatal outcomes at birth and at any time until discharge.

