### Exclusion criteria

Women will be excluded if any of the outcomes (including recurrent eclamptic seizures) occurs prior to testing or if informed consent could not be obtained on time or if the mother does not have a good understanding of spoken and written English and a translator is unavailable.

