Ideally, to develop a prediction model, we would like to observe outcomes in a cohort of women who receive no clinical management at all to be able to predict the likelihood of an adverse outcome independent of clinical management. Clearly, this is unethical and all women who present with pre-eclampsia receive clinical management, but such clinical decisions also affect maternal outcomes. Thus, in the development of our prediction model, we must recognise the importance of accounting for current clinical management; however, this is currently an under-researched methodological issue. By including effective treatment measures such as use of anti-hypertensives and magnesium sulphate predictor variables, and delivery before 34 weeks as a component of the composite outcome, we plan to negate some of the bias arising from treatment paradox in prediction models [23].

There is no obvious single outcome measurement that determines clinical management in early-onset pre-eclampsia. As the risk of more than one outcome needs evaluation simultaneously, we have chosen a composite measure consisting of several complications [37]. The composite outcomes are constructed by including those components whose underlying biology is similar [38].

To show that the PREP prognostic model is valuable, it is not sufficient to show that it successfully predicts outcome in the initial development data even after having it being internally validated. We need evidence that the model performs well for other (external) patients. The resulting geographical and domain validation will enable us to assess the prognostic performance and the generalisability of the model.

Our prediction model plans to use rigorous statistical methods to develop the model and assess accuracy; undertake a formal validation in external datasets (PIERS and PETRA); use unambiguous definitions of predictors and reproducible measurements using methods available in clinical practice; adjust for current clinical management; obtain input from patient focus groups and produce personalised estimates of risk, which enable patients and clinicians to make more informed decisions on management aspects like continuing the pregnancy or delivery of a preterm baby.

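### The two management-at-baseline predictors may be set by treatment started up to a day after diagnosis, while the survival model is already counting failures

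*Protocol article*

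**What the plan says.** In the protocol article, Table 2 (Candidate variables for inclusion in the model) has a block for management at baseline with two yes/no items: "Administration of oral and/or parenteral anti-hypertensives (ongoing or commenced within 1 day of diagnosis) (yes/no" and "Administration of magnesium sulphate (commenced before or within 1 day of diagnosis) (yes/no". The text above the table says that interventions applied between recruitment and outcome onset are collected as well.

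The Objectives state the primary aim as a model "for assessment of the risk of adverse maternal outcomes at 48 h and by discharge". Under Statistical analysis, the survival model is for adverse maternal outcomes "at various time points from diagnosis up to 34 weeks of gestation, including by 48 h after admission"; the by-discharge outcome has a separate logistic model. Under Model development, "failure event is defined as an adverse outcome or delivery occurring before 34 weeks of gestation".

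The Exclusion criteria deal with early outcomes in one way: "Women will be excluded if any of the outcomes (including recurrent eclamptic seizures) occurs prior to testing". The article states no landmark, no time-dependent covariate and no restriction to women still event-free at 24 h.

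**The concern.** A predictor for a model used at diagnosis should be known at diagnosis. These two items are labelled baseline but can change from no to yes during the next day, while failures are already accruing. Two things can go wrong.

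- **Immortal time.** A woman who fails at hour 6 cannot start treatment at hour 18, so she stays coded untreated. This pushes the hazard ratio below 1 even if treatment does nothing.
- **Reactive starts.** Treatment begun because the woman is deteriorating, or because delivery has been decided, is partly a marker of the outcome, since delivery before 34 weeks is itself a failure. This pushes the hazard ratio above 1.

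Either way, the coefficient partly reflects events after time zero, and a user at the bedside does not fully know the value to enter. The bootstrap described under Model development repeats the selection in resamples that carry the same coding, so its optimism estimate cannot detect the problem.

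**Working it through.** **Check on the article's own count.** Maternal candidates in Table 2: 3 + 1 + 3 + 6 + 7 + 2 = 22, which matches the 22 under Sample size considerations. The two management items are therefore among the predictors entering selection. The article gives no 48-h event rate, no proportion treated and no distribution of start times, so everything numerical below rests on assumed inputs.

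**Overlap.** The predictor window after diagnosis is 24 h and the horizon is 48 h. If diagnosis and admission coincide, 24/48 = 50% of the horizon is shared. This is the maximum: the horizon is worded from admission, so the overlap shrinks if admission follows diagnosis and vanishes if it follows by a day or more.

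**Share of 48-h events inside the overlap.** With a constant hazard and 48-h risk p, the share in the first 24 h is [1 − (1 − p)^0.5] / p:

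- p = 5%: 0.51
- p = 20%: 0.53
- p = 40%: 0.56

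**Immortal time alone.** Take a treatment with no effect and hazard h = −ln(1 − p)/48. Let q be the fraction of women destined for treatment and b the fraction of those already treated at time zero; the rest start uniformly over 0–24 h unless they fail first. The probability of having started by t is F(t) = b + (1 − b)·min(t/24, 1). Per woman over 48 h:

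- events coded treated: E1 = q ∫ F(t) h e^(−ht) dt
- hours coded treated: M1 = q [∫ F(t) t h e^(−ht) dt + 48(1 − p)]
- totals: E = p and M = p/h
- apparent rate ratio = (E1/M1) / [(E − E1)/(M − M1)]

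Worked case, p = 20%, q = 20%, b = 0: h = 0.00465, E1 = 0.0292, M1 = 8.52, E − E1 = 0.1708, M − M1 = 34.50. The rates are 0.00343 and 0.00495 per hour, a ratio of 0.69 where the truth is 1.

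| 48-h risk | Destined for treatment | None treated at time zero | Half treated at time zero | 80% treated at time zero |
|---|---|---|---|---|
| 20% | 20% | 0.69 | 0.84 | 0.94 |
| 20% | 40% | 0.63 | 0.80 | 0.92 |
| 40% | 20% | 0.68 | 0.84 | 0.93 |
| 40% | 40% | 0.61 | 0.79 | 0.91 |

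With status fixed at time zero (b = 1) the ratio is 1.

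**Reactive starts.** A simulation (400,000 women, constant hazard, 48-h risk 5–40%) assumed that half of the events in the first 24 h trigger a start, with a low background of unrelated starts (exponential, mean 240 h, so 1 − e^(−24/240) = 9.5% by 24 h if event-free). A null treatment then showed a risk ratio of 2.1 to 3.7 and a C-statistic of 0.61 to 0.62 for that item alone, against true values of 1.0 and 0.50. The direction is opposite to that in the table.

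**The case against.** The Discussion gives a reason for having treatment in the model: "By including effective treatment measures such as use of anti-hypertensives and magnesium sulphate predictor variables", together with delivery as an outcome component, is meant to offset the treatment paradox. That stands as a reason to include treatment. It says nothing about measuring treatment after the origin.

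Clinicians complete a management plan at baseline, so some imminent starts may be known when the model is used. That is fair for planned early starts, but the definition also admits unplanned starts later in the day.

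Both items explicitly include treatment already in place. Those women contribute no immortal time, so the 0.61–0.69 range is an upper-end illustration. If 80% are treated at time zero, the distortion from this mechanism is modest. Only two of 22 candidates are affected, and backward selection at p < 0.15 may drop either.

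A reader might infer that both coefficients are biased in a known direction and that performance is certainly inflated. The article does not support that: the two mechanisms oppose each other and may partly cancel, and the C-statistic of one item alone is not its gain over the other 21. A reader might also infer that the overlap is always half the horizon. The article does not support that either, because it names both diagnosis and admission and no rule ties them together.

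**Conclusion.** The point holds as a timing fault in a stated definition. Because the article fixes the predictor window, the origin and the failure event, and they conflict, this is not a detail left to an analysis plan. As written, information from up to 24 h after diagnosis can enter a primary model whose main short horizon is 48 h. The coefficients are open to bias of uncertain net direction, and apparent performance may be inflated without internal validation showing it.

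The size cannot be settled from the article. Under a constant hazard and the assumed rates, immortal time alone moves a null rate ratio to between 0.61 and 0.94, depending mainly on how many treated women were already on treatment at time zero; reactive starts would move it above 1. The effect is weaker for the by-discharge logistic model, where outcomes in the first day are a smaller part of the whole. It should be corrected before the models are fitted.

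**What to change.** 1. State a single time origin for the survival model, reconciling diagnosis and admission in the Statistical analysis section.
2. Code both predictors as treatment in place at or before that origin, removing the one-day allowance.
3. Treat later starts as the post-recruitment interventions the study already collects, not as baseline predictors.
4. Report a sensitivity analysis that omits both items.

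A 24-h landmark would also remove the overlap but is not advised for the primary 48-h model. At assumed risks of 20–40% and a constant hazard it would drop about 53–56% of the 48-h events, and it would answer a different question from the stated objective.

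The cost is two changed data definitions and one added analysis; nothing in clinical management changes. Fewer women will be coded as treated, and the apparent C-statistic may fall. Recoding needs treatment start times or status at baseline, and the article does not say that either is recorded, so this should be confirmed first.
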